# Deinstitutionalization from the perspective of community-dwelling adults with a severe mental illness in Amsterdam: a cohort study protocol

**DOI:** 10.1186/s12889-022-13291-w

**Published:** 2022-05-12

**Keywords:** Deinstitutionalization, Severe mental illness, Community-dwelling, Recovery, Quality of life, Societal participation, Cohort study, Study protocol

## Abstract

**Background:**

People with a severe mental illness (SMI) increasingly receive ambulatory forms of care and support. The trend of deinstitutionalization accelerated in the Netherlands from 2008 and onwards without sufficient understanding of its consequences. The study protocol herein focuses on deinstitutionalization from the perspective of adults with an SMI living within the community in Amsterdam and aims at delivering better insight into, amongst others, their recovery, quality of life, societal participation and needs for care and support.

**Methods:**

A cohort design will be used. A representative sample of community-dwelling adults with an SMI, including those in care (*n* = 650) and not in care (*n* = 150), will be followed over time. During a two-year time period, participants will be interviewed twice using a wide-ranging set of validated instruments. Interview data will be matched with administrative data about the care process, as retrieved from their patient files. Primary outcomes are changes over time in recovery, societal participation and quality of life, controlled for the occurrence of adverse life-events during follow-up. Additionally, prevalence estimates of and associations between social functioning, safety and discrimination, substance use and health indicators will be investigated.

**Discussion:**

The study protocol aims at delivering a comprehensive insight into the needs of community-dwelling adults with an SMI based on which ambulatory care and support can best be provided to optimally promote their social recovery and well-being.

## Background

In many high income countries, including the Netherlands, an increasing proportion of people with a severe mental illness (SMI) live independently, within the community. Instead of residing in a long-stay clinical setting in psychiatric institutions, these ‘outpatients’ receive ambulatory mental health care in addition to social and economic support when required. This trend is historically and internationally referred to as deinstitutionalization. In the Netherlands, deinstitutionalization gained new impetus in the year 2008 and onwards. In 2013, the Dutch Ministry of Health, Welfare and Sports, the mental health care sector and health insurance companies agreed to reduce the number of clinical psychiatric beds designated to people with an SMI by a third in the year 2020, with the bed-count in 2008 being the reference [1, 2]. Two underlying rationales guided the agreement. First, ambulatory mental health services at home would be more beneficial with respect to recovery of people with an SMI, specifically social and personal aspects of recovery. Second, ambulatory mental health services at home would be more cost-effective than the provision of long-stay inpatient care services.

In parallel, a number of changes in legislation transferred the responsibility regarding the public mental health care system (Social support act. In Dutch: *Wet maatschappelijke ondersteuning* 2015) [3] and the social inclusion of vulnerable groups (Social support act; Participation act. In Dutch: Participatiewet 2018) [4] from the national government to municipal (local) governments. Municipalities were tasked with two new responsibilities, namely providing ambulatory support to vulnerable populations (e.g., nursing care for home-dwelling elderly, reintegration of the long-term unemployed, and social recovery of persons with mental and/or physical disorders and disabilities) and developing and installing local policy measures required to guide the process of deinstitutionalization.

As such, whereas until fairly recently the treatment of people with an SMI primarily focused on improving their mental and physical functioning, present-day treatment plans dedicate additional focus to building and maintaining a satisfactory informal and formal social life [5, 6]. The extent to which people with an SMI are able to satisfy such social needs depends strongly on the support that relatives/friends and, on occasion, mental health care professionals are willing and able to provide. For varying reasons, however, a considerable proportion of people with an SMI are unable to capitalize the (informal) social support that is offered to them.

A vast literature shows that people with an SMI, especially those living within the community, constitute a vulnerable population with respect to several adverse, and often intertwined, outcomes. Pivotal is that people with an SMI are prone to experience difficulties regarding social participation (i.e. (paid) work and education) [7, 8] and social inclusion [9], which in itself are known to be associated with, amongst others, quality of life and the extent to which their health care and support needs are met [10, 11]. Within the target population of people with an SMI, a substantial proportion of people present with a psychotic or mood/anxiety disorder, while substance use disorders are also highly prevalent (i.e. dual diagnosis disorder) [12], associated with unhealthy life-style behaviors [13], poor physical health and overall suboptimal well-being [14]. Importantly, people with an SMI are also a high risk group with respect to experiencing discrimination [15, 16], stigmatization [17, 18], social exclusion [19] and victimization [20–24], each of which is detrimental to their social participation. Such outcomes are strongly associated with the concept of recovery of people with an SMI, which is increasingly broken down into clinical, functional and personal recovery [25–27]. Clinical recovery concerns the degree of symptomatic symptomatology [28]. Functional recovery refers to functional outcomes with respect to important life-domains such as work, daytime activities, societal participation, housing, social relations and daily living tasks. Personal recovery, or subjective recovery, refers to living a meaningful life such as captured by the CHIME-framework: connectedness, hope and optimism, identity, meaning in life, and empowerment [29]. The vulnerability of this target population constitutes the current responsibility of local government (i.e. municipalities), in collaboration with private care and support services, to provide this group with the necessary support in order to maintain satisfactory living conditions. In this respect, deinstitutionalization of people with SMI concerns more than the mere redesign of mental health care services. Its impact is much wider and multifaceted and it affects a large variety of stakeholders involved in the target population of people with SMI. Deinstitutionalization requires each of these stakeholders to reassess their role, interest and position in local care and support networks for people with an SMI.

Despite evident changes that are expected to result from the ongoing deinstitutionalization in the Netherlands, there is not yet a clear view on its effects and implications from the perspectives of the most important stakeholders. These primary stakeholders are 1) people with an SMI themselves, 2) their relatives and friends (i.e. informal providers of care and support), 3) mental health care providers and social services including their professionals, 4) neighborhoods and fellow residents, and 5) local government. Some recent initiatives and research projects have already been carried out to scrutinize the consequences of deinstitutionalization in the Netherlands. However, they did so primarily from a national or regional perspective [30–33]. Notwithstanding their merit, these studies did not address the specific questions and topics concerning deinstitutionalization that emanate from the combined perspectives of each of the aforementioned stakeholders and from the level of the municipality.

Against this background, the public health service of Amsterdam, in close collaboration with Amsterdam’s two largest mental health care institutions, initiated a research program ‘Deinstitutionalization Amsterdam’ (in Dutch: *Ambulantisering Amsterdam*). This research program aims at providing more insight in the process, results and effects of deinstitutionalization from the perspectives of people with an SMI, their close relatives and friends, their neighbors and neighborhoods, the mental health care institutions, social services and welfare organizations involved, and the municipality. The main question of the research program is: *How can ambulatory care and support for community-dwelling adults with a severe mental illness best be provided to optimally promote their social recovery?*

The research program is modular. It consists of multiple interrelated research projects. Each of these projects addresses deinstitutionalization from one of the aforementioned perspectives. The current study protocol applies to the ‘client study’ of the program, that focuses on the perspective on deinstitutionalization from its main stakeholder: community-dwelling adults with an SMI. More specifically, the protocol lays out the study design by means of which a representative research cohort of people with an SMI in Amsterdam will be assembled (i.e. inclusion and exclusion criteria) and followed over time. Additionally, the protocol describes the process of participant recruitment, the instruments that will be administered, the study’s primary outcome measures and the statistical analyses that will be performed. Furthermore, the protocol specifies how the following research questions will be addressed:Which trends in the development of community-dwelling people with an SMI concerning their quality of life, recovery, daily functioning and societal participation can be observed over the course of time?Which needs of community-dwelling people with SMI are most important with respect to their recovery and societal participation?How are these needs addressed and accommodated by formal and informal providers of ambulatory care and support?How can the provision of community-based ambulatory care for people with an SMI be described with respect to treatment compliance, therapeutic alliance and frequency/timeliness of care consults?What is the prevalence and incidence during follow-up of personal crises and escalations, including psychological crises, compulsory (clinical) treatment and victimization, among this population?

## Methods

### Study design

The Deinstitutionalization Amsterdam Client-study is a cohort study that started in December 2017. The study is planned to include approximately 800 adults with an SMI. The study population is designed to be representative for the target population of community-dwelling adults with an SMI at the city level, the level of the city-districts and the level of the city’s quarters (i.e. combined neighborhoods). To acquire a better insight into developments in the functioning and recovery of community-dwelling adults with an SMI and their associated needs for care/support, a comprehensive set of measurement instruments will be administered twice, with a two-year time interval, by means of semi-structured interviews. Also, the occurrence of adverse life-events during follow-up will be associated with developments in people’s functioning (i.e. social recovery and societal participation) over the course of time. Additionally, information about the care processes during that time will be retrieved from participants’ patient files.

### Setting

The study is situated in Amsterdam, the Netherlands. Internationally, the prevalence of SMI in the general population is estimated to vary between 0.5–2.9% according to, amongst others, population density, age distribution, social economic indicators, the number of (ethnic) minorities and the level of social cohesion [34–38]. Concerning specifically Amsterdam, reliable figures about the number of inhabitants with an SMI are lacking. The most recent 12 month-prevalence estimates vary between 1.6% [31] and 2.0% [30, 39], equaling an SMI population of between 7923 and 9827 adults within the municipality, of whom approximately 90% are considered community-dwelling and 10% to reside in long-term clinical settings [40].

The city of Amsterdam is subdivided into 8 administrative districts of which 7 residential districts and 1 industrial/harbor district. Together, the residential districts consist of 476 distinct neighborhoods, conglomerated into 99 quarters (or combined neighborhoods). Participants will be sampled and recruited at the level of quarters. As such, the resulting sample is designed to be representative at the level of the city, the city-districts and the quarters. From each of the residential districts, the two largest quarters are selected (based on population size, ranging from 12,946 to 26,787 registered residents). Together, these 14 quarters comprise 104 neighborhoods, 4437 unique postal codes and 237,157 inhabitants [38]. Within these quarters, prevalence estimates of SMI range between .02 and 3.08% [36] and an average SMI prevalence of 1.6% of the adult population of these quarters is assumed.

### Participants

Participants will be recruited on the basis of three inclusion criteria: age, SMI and location. The age-criterion is chosen to align the study population with the patient populations of mental health care providers and care system for adults. Although deinstitutionalization also applies to minors (< 18) and the elderly (65+), these populations are serviced by care providers in other care networks: youth [41] services and elderly [41] care, respectively. Integration of the care systems for these different age-groups is, at the time of this writing, still in its infancy. The scope of the current study is therefore limited to adults only (age 18–65).

The SMI criteria as postulated by the ‘Dutch consensus group EPA’ [31] (EPA is the abbreviation of Ernstige Pychiatrische Aandoeningen which translates to SMI) are applied. These criteria are as follows:there has to be a psychiatric disorder that requires care/treatment;the disorder is directly related to severely impaired social/societal functioning;the functioning impairments are both cause and effect of the psychiatric disorder at play;the disorder is not transient in nature (i.e., it is structural or chronic for at least 2 years);coordinated care from professional care providers, embedded in local health care networks, is indicated to perform and effectuate the treatment plan for the psychiatric disorder.

This SMI-definition matches international SMI-criteria to a large extent [35, 36, 42], but not completely. Although a consensual definition is SMI is lacking, SMI is commonly understood as a function of three “D’s”, diagnosis, disability and duration [43, 44]. In contrast, the definition used in the current study focuses on the functional impairments and its effects on daily activities for which people with SMI need care and support. This results in a more inclusive definition of SMI in which no diagnosis is a priori excluded or included. More specifically, certain psychiatric symptoms, such as those associated with schizophrenia spectrum disorders (e.g., delusions and hallucinations), are considered to belong exclusively to the target population of people with an SMI. Other symptoms have been demonstrated to occur at different rates among people with an SMI. For example, poly drug use, personality disorders and pervasive developmental disorders are prevalent symptoms among people with an SMI as well. Mood and anxiety disorders and alcohol abuse, on the other hand, are relatively infrequent [34]. In addition, people with an intellectual disability or a physical impairment and people with dementia may also meet the aforementioned SMI-criteria. However, they do so only if a normative need for mental health care regarding psychiatric comorbidity is established.

#### Exclusion criteria

The following exclusion criteria will be applied:people with an intellectual and/or physical disability who are not in need of mental health care for co-morbid psychiatric disorders;people who suffer from dementia and who are not in need of mental health care for co-morbid psychiatric disorders;people who meet all inclusion criteria but whose formal postal code of their home address matches those of long-term clinical locations of mental health care providers (i.e. not community-dwelling patients);people whose proficiency in either Dutch or English is insufficient to be interviewed, and people who cannot be approached due to other mental health or social problems.

Within the larger population of community-dwelling adults with an SMI, the study differentiates between three cohorts. First, the ‘in-care cohort’ consists of adults with an SMI who receive ambulatory mental health care. Second, the ‘not-in-care cohort’ is formed by adults with an SMI who do not receive specialized mental health care from a formal mental health care provider yet may receive social welfare/support. Third, the ‘LZA-cohort’ are participants of a former longitudinal cross-sectional study into long-term care-dependent psychiatric patients in Amsterdam, carried out in 2005 and 2012 by Amsterdam’s largest mental health care providers Arkin and GGZ inGeest (in Dutch: the Langdurige zorgafhankelijkenstudie or LZA-study). This study focused on the psychological and social functioning and quality of life of people with a chronic SMI [32, 45]. Participants of the LZA-study who provided written consent to be re-approached were eligible to participate in the current study. The reason to include this LZA-cohort is that the current study utilizes a similar set of instruments which enables a third measurement for the LZA-study, providing insight in long-term (2005–2020) developments of this subgroup within the population of people with SMI.

With respect to the in-care and not-in-care cohorts, their relative proportions within the total SMI-population in Amsterdam are approximately 76 and 24%, respectively [30]. Furthermore, around 90% of both groups lives independently (i.e. community dwelling). In-care participants will be recruited at the two largest mental health care providers in Amsterdam, Arkin and GGZ inGeest. Together, these organizations are estimated to provide care/treatment to two thirds of the total in-care population of people with an SMI in Amsterdam [39]. The remaining 33% of the in-care SMI-population, those who receive mental health care from one of several other (small) providers, will not be included as we expect to obtain a representative sample of the in-care population from the selected service providers. Moreover, recruiting participants at numerous care providers would require a disproportional effort and is therefore considered unfeasible. The ‘not-in-care’ participants will be recruited at a variety of social welfare and social support organizations in Amsterdam, including organizations that target the homeless (e.g., HVO-Querido, Leger des Heils, Cordaan, Volksbond). In this group, the SMI-criteria will be assessed during the interview.

As such, on the basis of 1) the assumed average SMI prevalence of 1.6% among the adult population of the selected quarters (237,157 * 1,6% = 3795 people), and 2) the proportion of adults with an SMI who are registered as a mental health care patient (76%, *n* = 2884), and 3) of whom at one of the two main mental health care providers in the city (66%, *n* = 1903) and 4) the proportion within this group who live independently (i.e. community dwelling) (90%), the in-care cohort is estimated to consist of 1739 adults with an SMI. On the basis of the aforementioned proportions, the not-in-care cohort is estimated to consist of 820 people. The LZA-cohort potentially consists of 157 former LZA-participants who gave permission to be re-approached. Based on expected response rates of 33% in the in-care cohort, 20% in the not-in-care cohort and 50% in the LZA-cohort, the study sample will consist of approximately 800 participants. Figure 1 presents a flowchart depicting the composition of the study population.

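### The 1.6% adult prevalence of SMI is applied to all 237,157 inhabitants of the selected quarters, so the recruitment frame and the expected sample are overstated by an amount the article does not let the reader fix

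*Protocol article*

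**What the plan says.** All references are to the protocol article.

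- **Setting** describes the base: "Together, these 14 quarters comprise 104 neighborhoods, 4437 unique postal codes and 237,157 inhabitants". The quarters were chosen as the two largest in each residential district, "based on population size, ranging from 12,946 to 26,787 registered residents". No age limit is attached to either count.
- The same section states what the prevalence refers to: "an average SMI prevalence of 1.6% of the adult population of these quarters is assumed".
- **Participants** restricts eligibility by age: "The scope of the current study is therefore limited to adults only", with the range 18 to 65 given directly after. Minors and the elderly are described as served by other care networks.
- The sizing paragraph, under **Exclusion criteria**, multiplies the two: "the assumed average SMI prevalence of 1.6% among the adult population of the selected quarters (237,157 * 1,6% = 3795 people". It then takes 76% registered in care (2884) and 66% of those at the two main providers (1903). The last step is "live independently (i.e. community dwelling) (90%), the in-care cohort is estimated to consist of 1739 adults with an SMI". The not-in-care frame is put at 820 and the LZA cohort at 157. Response rates of 33%, 20% and 50% lead to about 800 participants.
- The paragraph before it gives the two providers' share as two thirds and excludes a remaining 33%.
- **Bias** sets an aim of including at least 30% of the people with SMI in the selected quarters.

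**The concern.** A prevalence has to be multiplied by the population it refers to. Here the rate is per adult and the multiplier is a count of inhabitants, and no later step removes minors or people over 65. Every figure downstream, apart from the fixed 157 of the LZA cohort, carries the excess in proportion.

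The chain is the only basis the article gives for expecting about 800 participants (650 in care and 150 not in care in the Abstract). The size of the SMI population in the quarters also determines whether the 30% coverage aim is met, and that aim is part of the argument for representativeness. If the overstated frame is used as a denominator, response and coverage will look lower than they were.

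**Working it through.** **1. The article's own figures.**

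- 237,157 × 0.016 = 3794.5 (3795 stated)
- 3795 × 0.76 = 2884 (matches)
- 2884 × 0.66 = 1903 (matches)
- 1903 × 0.90 = 1713 (1739 stated)
- 3795 × 0.24 × 0.90 = 820 (matches)
- Sample with 1739: 0.33 × 1739 + 0.20 × 820 + 0.50 × 157 = 573.9 + 164 + 78.5 = 816
- Sample with 1713: 565.3 + 164 + 78.5 = 808

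Both totals agree with about 800. In care plus LZA is 652 (or 644) and not in care is 164, close to the 650 and 150 of the Abstract.

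**2. Where 1739 comes from.** The complement of the excluded 33% is 67%, and 2884 × 0.67 × 0.90 = 1739. Two thirds would give 1730. So 66% is printed and 67% fits the result. The gap is 26 people in the frame (1.5%) and 0.33 × 26 ≈ 8 in the sample.

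**3. Effect of the base.** Let s be the share of inhabitants aged 18 to 65, and assume that the 1.6% applies in that age range. The in-care and not-in-care terms scale with s and the LZA term does not:

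- with 66%: sample = 729.3 × s + 78.5
- with 67%: sample = 737.9 × s + 78.5

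The article gives no value for s, so the rows below 1.00 are assumptions. Frames and required response rates use the printed 66%.

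| s | People with SMI | In care | Not in care | Sample (66%) | Sample (67%) | In-care response needed | Not-in-care response needed |
|---|---|---|---|---|---|---|---|
| 0.60 | 2277 | 1028 | 492 | 516 | 521 | 55.6% | 30.5% |
| 0.70 | 2656 | 1199 | 574 | 589 | 595 | 47.7% | 26.1% |
| 0.80 | 3036 | 1370 | 656 | 662 | 669 | 41.7% | 22.9% |
| 0.90 | 3415 | 1542 | 738 | 735 | 742 | 37.1% | 20.3% |
| 1.00 | 3795 | 1713 | 820 | 808 | 816 | 33.4% | 18.3% |

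The required rates are (650 − 78.5) / in-care frame and 150 / not-in-care frame, counting the expected 78.5 LZA participants towards the 650. The stated rates are 33% and 20%.

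**4. Share needed for 800.** (800 − 78.5) / 729.3 = 0.989 with 66%, and 721.5 / 737.9 = 0.978 with 67%. Nearly every inhabitant would have to be aged 18 to 65.

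**5. Is 237,157 perhaps already a count of adults?** For the city, Setting reports "equaling an SMI population of between 7923 and 9827 adults within the municipality". At the 1.6% and 2.0% given there, this implies 7923 / 0.016 = 495,188 and 9827 / 0.02 = 491,350 adults, two nearly equal bases. If 237,157 were adults too, 14 of 99 quarters would hold 237,157 / 495,188 = 47.9% of the city's adults. The selected quarters would average 237,157 / 14 = 16,940 and the other 85 would average (495,188 − 237,157) / 85 = 3,036.

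**The case against.** The strongest defence is that the arithmetic works. The 820 follows exactly, and about 800 follows from the printed inputs whichever provider share is used. This stands: a reader might infer from the mismatch at 1739 that the sample does not follow from its inputs, and it does. The fault is in one input.

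A reader might also infer that the 90% step was miscalculated. The article does not support that, because 1739 is reproduced exactly with 67% and 90%. What is inconsistent is the provider share.

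It can be said, too, that the comparison with the city total does not prove that 237,157 includes non-adults. That is right. The 14 quarters were chosen for their size, so a gap is expected, and the article gives no sizes for the other 85. The comparison makes an adult count very implausible but does not exclude it. The point rests mainly on the wording, which says inhabitants and registered residents here and adults for the city figure.

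Finally, the chain is a feasibility forecast and not a power calculation, and by the recruitment dates given under Figure 1 baseline recruitment had ended by January 2022, before publication. A correction cannot change recruitment. The article also does not say that 1739 and 820 will be the denominators for reported response, and counts of people approached through the care teams and services could serve instead. This limits the consequence to the stated frame, the expected sample, and any coverage or response figure that uses them.

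**Conclusion.** The denominator error holds as the article is worded. The 3795, 1739 and 820 are overstated by the share of residents outside ages 18 to 65, and no other section resolves the mismatch. The direction is clear, but the size cannot be fixed from the article. Under an assumed share of 60% to 90%, the stated response rates give about 516 to 735 participants (printed 66%), and about 800 is reached only at a share of about 98% to 99%. These figures also assume that the 1.6% applies evenly within the eligible ages.

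A reader might go further and conclude that the study missed its target or that any later response rate is wrong. Neither follows: the stated response rates are expectations, actual response may have differed, and the reporting denominator is not stated.

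The 66%/67% inconsistency is minor, at about 8 participants. Overall, this is an inexpensive correction that should be made, because the expected sample and the 30% coverage aim depend on the size of this population.

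**What to change.** 1. Replace 237,157 with the number of registered residents aged 18 to 65 in the 14 quarters, from the same municipal source. If the figure is already restricted by age, say so and give the range.
2. Use one share for the two main providers throughout (66%, two thirds or 67%), and print the intermediate count that belongs to it.
3. Rerun the chain and Figure 1, and restate either the expected sample at 33%, 20% and 50% or the response rates that 800 implies.
4. Use the corrected frame for the 30% coverage aim and for any response figure based on it.

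The cost is one table look-up, a recalculation and revised wording. No data collection or analysis changes. With the age restriction applied, the stated expected sample becomes less favourable, while coverage computed on the smaller frame becomes higher for the same number of participants.
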